##### Blood markers of inflammation

C- reactive protein and white cell count will be measured.

##### Health economic outcomes

An exploratory analysis will be made of the cost of the exercise intervention, and the net monetary benefit on health care costs and health care interactions that arise during the study will be calculated.

##### NCT toxicity

Rates of NCT toxicity, tolerance and compliance will be collected.

##### Patient and public involvement (PPI)

Patient and public volunteers are members of the trial steering committee, and their experience and input were used to help shape the study design. Volunteers attend quarterly trial steering meetings and receive monthly newsletters and trial management meeting minutes. They will assist with trial delivery and conduct as well as trial reporting. Additionally, they will guide our dissemination plan using social media, presentation at conferences, dissemination to patient advocacy groups and journal articles.

##### Safety

Adverse events are recorded in the relevant case report form by the lead site researcher. Fatal or life-threatening serious adverse events are reported within 24 h of the research team becoming aware of the event. The serious adverse events form documents the nature of the event, date of onset, severity, corrective therapies given, outcome and causality (i.e., unrelated, unlikely, possibly, probably or definitely). Any queries relating to adverse event reporting will be directed to the principal investigator.

#### Data analysis

##### Sample size calculation

The sample size calculation was based on results from a recent publication by Minnella et al. [46] who identified a pre-operative increase in 6MWT of 60 m from a baseline score of 450 m, which is an improvement of approximately 13%. Assuming a similar baseline score, a 15% difference can be detected with a *p* value of 0.05 and power of 80% with a sample of 26 participants with full data in the two groups. With an anticipated 20% drop out, recruitment of 62 participants is anticipated.

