Objectives	7	The aims of this study were to evaluate the following hypotheses: Primary hypothesis: A structured community-based exercise programme compared with a usual care control group (usual care – no formal exercise training) will result in a clinically significant increase in cardiorespiratory fitness assessed using a 6-min walk test between the baseline and the pre-surgery time point. Secondary hypotheses: A structured community-based exercise programme compared with a usual care control group (usual care – no formal exercise training) will result in improvements in other physical health outcomes assessed using upper and lower body strength test, activity behavior monitoring, body mass index, frailty, and psychological health questionnaires assessed at 5 time points baseline, post NCT, pre-surgery, 4 weeks and 10 weeks after surgery as well as semi-structured interviews assessed pre and post-surgery. Exploratory Endpoints: Post-operative morbidity, comprehensive complication index, hospital length of stay, nutritional status, immune and inflammatory markers, cancer staging, response to NCT and a medico-economics analysis of cost effectiveness of the exercise intervention on reducing health care costs and burden additionally rates of NCT toxicity, tolerance and complicance will be measured.	7
Trial design	8	Parallel group randomised 1:1 controlled multi-centre trial.	9

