Outcomes	12	The primary endpoint is cardiorespiratory fitness measured by the 6-min walk test between the baseline assessment and the pre-surgery time point. Secondary endpoints include the measurement of cardiorespiratory fitness, physical health assessed using upper and lower body strength tests, activity behaviours, body mass index, and frailty; and psychological health assessed using health-related quality of life questionnaires and semi structured interviews. Exploratory endpoints include post-operative morbidity, comprenhensive complication index, hospital length of stay, nutritional status, immune and inflammatory markers, cancer staging, response to NCT, medico-economics analysis of cost effectiveness of the exercise intervention on reducing health care costs and burden additionally rates of NCT toxicity, tolerance and compliance.	13
Participant timeline	13	Outcome measurements are taken for all participants at baseline, post-NCT, pre-surgery, 3 days post-surgery, 5 days post-surgery, 4 weeks post-surgery and 10 weeks post-surgery.	7
Sample size	14	The sample size calculation was based on results from the Minnella et al. study, which identified a pre-operative score gain in 6 MWT of 60 m from a baseline score of 450 m (standard deviation 85 m), which is an approximate 13% improvement. Assuming a similar baseline score, a 15% score gain can be detected with *p* value of 0.05 and power 80% with a sample of 26 participants with full data in two groups. With an anticipated 20% drop-out, recruitment of 62 participants is anticipated.	18
Recruitment	15	Inclusion of three clinical sites and seven exercise sites with the additional option of a home programme.	7

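### Minor arithmetic error: after the stated 20% drop-out, 62 recruits leave about 50 participants with full data, not the 52 the plan needs

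*Protocol article*

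**What the plan says.** The Sample size calculation section of the Protocol article starts from a baseline 6-minute walk distance of 450 m. It says that "a 15% difference can be detected" at a significance level of 0.05 and "power of 80% with a sample of 26 participants with full data in the two groups". The recruitment target follows at once: "With an anticipated 20% drop out, recruitment of 62 participants is anticipated".

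Item 14 of Table 2 (the SPIRIT table) repeats the calculation. It adds the spread, a "baseline score of 450 m (standard deviation 85 m", gives the number as "a sample of 26 participants with full data in two groups", and states the same target: "With an anticipated 20% drop-out, recruitment of 62 participants is anticipated".

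Two further statements fix the setting. Item 8 of Table 2 describes a "Parallel group randomised 1:1 controlled multi-centre trial", and the Statistical analysis section makes an independent-groups t-test the primary analysis.

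**The concern.** A recruitment target should be large enough that, once the expected proportion has dropped out, the number the power calculation needs is still there. Here the number needed, the drop-out rate and the target are all stated, so they can be checked against each other, and they do not agree. The wording also leaves the reader to work out whether 26 is the number in each group or in both together.

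This is the only justification given for the trial's size, and it appears twice. If the target is too low for the plan's own drop-out rate, the trial would be expected to finish with fewer complete participants than it says it needs, and the same figures would pass into the final report.

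**Working it through.** **Inputs**

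- Target difference: 15% of 450 m = 0.15 × 450 = 67.5 m (Sample size calculation).
- SD: 85 m (Table 2, item 14). It is given beside the baseline score of the cited study. Using it for the pre-surgery score is an assumption.
- Alpha: 0.05. Sidedness is not stated. Two-sided is assumed because it reproduces the plan's 26; a one-sided 5% test would need only 20 per group (normal approximation).
- Power 80%, allocation 1:1, independent-groups t-test, drop-out 20%, target 62.

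**Step 1. Reproduce the 26.** The power of the t-test comes from the noncentral t distribution with noncentrality Δ / (SD × √(1/n₁ + 1/n₂)) and n₁ + n₂ − 2 degrees of freedom.

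- With 26 per group: 67.5 / (85 × √(2/26)) = 67.5 / 23.57 = 2.86 on 50 degrees of freedom. Power is 80.2%.
- 26 is the smallest group size that reaches 80%.

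The plan's figure is therefore reproduced as 26 **per group**, or 52 in total.

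**Step 2. Check the target.** To keep N completers when a proportion d is lost, recruit N / (1 − d).

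- Required: 52 / (1 − 0.20) = 65. With equal arms this becomes 66, since 33 × 0.8 = 26.4 per arm.
- Expected from the stated target: 62 × 0.8 = 49.6, or 24.8 per group. The shortfall is 52 − 49.6 = 2.4 completers.
- Loss that 62 can absorb: 1 − 52/62 = 16.1%.

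**Step 3. Where 62 may come from.**

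- Multiplying instead of dividing: 52 × 1.2 = 62.4.
- Starting from the normal approximation, which gives 25 per group: 50 / 0.8 = 62.5. This does not match the stated 26.

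The first is the likelier route. Neither makes 62 consistent with 26 per group and 20% loss.

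**Step 4. Power at 62 recruited and 20% lost, for 67.5 m.**

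| Completers | Power |
|---|---|
| 26 + 26 (as required) | 80.2% |
| 25 + 25 | 78.6% |
| 24.8 + 24.8 (expected) | 78.2% |
| 25 + 24 | 77.7% |
| Random loss, 31 per arm, each completing with probability 0.8 | 77.9% on average |

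By the normal approximation, 24.8 per group gives 79.9% and 26 per group gives 81.7%.

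**The case against.** The strongest reply is that the plan attaches its 80% to participants with full data and claims no power for the 62 recruited. That is correct. The power figure reproduces, and only the inflation step is wrong. A reader might infer that the trial's power statement fails or that the trial is materially underpowered. The documents do not support that: the loss is about 2 points, it almost vanishes under the normal approximation, and 62 still yields 52 completers if no more than about 16% are lost. The uncertainty about the SD is also larger than the gap between 78% and 80%. All of this limits the size of the point, but none of it makes 62 the right number for 20% drop-out.

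Two other inferences should be set aside.

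- A reader might read 26 as the total. The next sentence rules this out: 26 / 0.8 = 32.5, which is nowhere near 62, while 52 comes close. The wording is loose and worth tidying, but it does not describe a smaller trial.
- A reader might take the planned 67.5 m as an error because the cited study reported a gain of 60 m. The plan states both figures openly and chooses 15% as its target difference, which the abstract also names in the primary endpoint. The 60 m is described as an increase from baseline, and nothing in the document says it is a difference between arms. Choosing a larger target is a design decision, not an arithmetic slip.

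**Conclusion.** The point holds as a minor arithmetic error, wrong as written in both places. For 26 complete participants per group after 20% drop-out the target should be 65 (66 for equal arms), so 62 is 3 or 4 short. At the plan's own drop-out rate the trial would expect about 50 complete participants and about 78% power for 67.5 m, against 52 and 80%.

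The 65 follows from the plan's figures once 26 is taken as per group. The power figures rest on two assumptions that the article does not state: that 85 m is the SD of the pre-surgery distance, and that the test is two-sided at 5%. The error changes neither the primary test nor how the result would be analysed.

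**What to change.** In the Sample size calculation section and in item 14 of Table 2:

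1. Write the requirement as 26 per group (52 in total) with full data.
2. Keep 62, and say what it delivers. Either state that with 20% drop-out about 50 participants are expected to have full data, giving about 78% power for 67.5 m, or state that 62 allows for about 16% drop-out.
3. In the same sentence, name the two-sided test and say that the SD of 85 m is assumed for the pre-surgery score.

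The cost is one reworded sentence in two places and, under the first option, a slightly lower stated power. No participants are added. Raising the target to 65 or 66 would also remove the inconsistency, at the price of 3 or 4 more recruits, but the size of the loss does not require it.

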##### Statistical analysis

The analysis will be performed as an intention-to-treat analysis. No interim analysis will be conducted. Data validity will be conducted prior to analysis and corrected as appropriate.

The study population will be described separately for the two randomised groups using variables obtained at baseline. The variables will be described as mean (SD) and numbers (%) as appropriate.

The primary analysis of the primary outcome will be conducted using t-tests of independent group mean differences in 6MWT. The mean difference and 95% confidence interval will be reported and illustrated graphically. Individual change in 6MWT will be calculated from baseline and compared at different time points using t-tests.

The secondary analysis of the primary outcome will use mixed-level analysis with intervention group, time point and interaction of intervention and time points. This analysis will include baseline score for the outcome measure as a covariate. The estimated parameter for the interaction variables will be interpreted as the difference-in-difference between the two groups over time. A separate analysis will explore potential differences in the intervention group between participants who received the intervention at a training centre and those who trained at home. This analysis will be expanded to include descriptive baseline variables such as sex and age. The secondary analysis will use mixed-level analysis and include baseline score and baseline characteristics as covariates.

The cost-effectiveness analysis will be conducted from a societal perspective over the duration of the trial period. No extrapolation of long-term economic outcomes is planned. The EQ-5D-5 L data reported at each time point will be used to estimate quality-adjusted life years using time-weighted utility scores. The utility scores will be calculated for each individual at each data point using the Irish scoring algorithm for EQ-5D-5 L [47]. The area under the curve denotes the QALY, and incremental QALY is determined as the mean group difference.

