### Study objectives

The primary objective of the PERIOP-OG trial is to demonstrate that a structured community-based exercise programme will result in a clinically significant increase in cardiorespiratory fitness pre-surgery when compared to a standard care control group. Cardiorespiratory fitness is assessed using a 6-min walk test (6MWT) at five timepoints in the trial:baseline, post-NCT, pre-surgery, and 4 weeks and 10 weeks after surgery.

Secondary aims include assessing whether exercise training improves other physical health outcomes: upper and lower body strength tests, activity behaviour monitoring, body mass index and frailty. Psychological health is assessed using a series of questionnaires: EQ-5D-5 L Health Questionnaire, Functional Assessment of Cancer Therapy (FACT-E), General Self Efficacy (GSE), Pearlin Mastery Scale (PMS), Surgical Fear Questionnaire (SFQ) and general optimism using the Life Orientation Test-Revised (LOT-R) tool as well as semi-structured interviews.

Exploratory end-points include assessment of post-operative morbidity (Clavien-Dindo classification and as agreed upon by the Esophagectomy Complications Consensus Group (ECCG) [28], the Comprehensive Complication Index, hospital length of stay, nutritional status (serum albumin, sarcopenia score and Foodbook-24), inflammatory markers, cancer staging and response to NCT and a medico-economics analysis of cost effectiveness of the exercise intervention on reducing health care costs and burden. Additionally, rates of NCT toxicity, tolerance and compliance will be measured.

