### Primary outcome

#### Cardiorespiratory fitness

The primary outcome is measurement of cardiorespiratory fitness using the 6MWT assessed at the pre-surgery timepoint. The 6MWT is performed with participants walking up and down a 20 m course marked by cones for 6 min under instruction to cover as much ground as possible. The number of laps completed is recorded. A standard set of instructions is used as per the European Respiratory Society guidelines. The 6MWT is a validated assessment of cardiorespiratory function in clinical populations [30, 31]. A systematic review in 2016 demonstrated that field tests may be able to predict post-operative outcome; however, further validation work is merited [32].

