##### Missing data

Participants with missing data either because of early drop-out, loss to follow-up or missed participation in the data collection can bias the results. By design, no data will be missing at baseline because only participants with complete baseline data will be randomised.

Missing variables in outcome measures will be handled according to instrument developers’ guidelines. As a general rule, if more than 20% of the items of an instrument are missing, the summary score will be assigned as missing. Missing data will be reported as part of the summary presentation of the raw data. Logistic regression will be used to explore whether participants with missing data have different characteristics than the completers or whether missing data can be assumed missing by random.

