**Methods: data collection, management, and analysis**			
Data collection methods	18a	The outcomes are listed in Table 1: Outcomes and assessment measures.	13
	18b	The participants are contacted by telephone during the intervention to promote participant retention and complete follow-up. Baseline data to be collected for participants who discontinue or deviate from intervention protocols, unless they withdraw consent.	13
Data management	19	Data will be double data entered, and data validation will take place according to the procedures set out in the data management plan and data validation plan. Prior to any statistical analysis, all variables will be checked for the number of missing values, impossible values and improbable values. Impossible and improbable values will be defined by clinical opinion. Improbable values will also include values that are outside three standard deviations of the mean value. Any questions regarding the data will go back to the data manager. Descriptive statistics will be calculated for all variables, and distributional assumptions will be checked.	20
Statistical methods	20a	The analysis will be performed as an intention-to-treat analysis. No interim analysis will be conducted. Data validity will be conducted prior to analysis and corrected as appropriate. This includes tabulation of discrete score values and graphical representation of continuous variables (e.g., histograms and box plots). The study population will be described separately for two randomised groups using variables obtained at baseline. The variables will be described as mean (SD) and numbers (%) as appropriate. The primary analysis of the primary outcome will be conducted as t-tests of independent group mean differences in 6MWT at each time point. The mean difference and 95% confidence interval will be reported and illustrated graphically. Individual change in 6MWT will be calculated from baseline and compared at different time points using t-tests. In addition, binary outcome variables indicating ability to walk more than the combined median distance at baseline will be constructed, and the group distribution will be tested at different time points using chi-squared tests.	18

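### Adjusting the primary 6MWT comparison for baseline would make it more efficient; the planned unadjusted t-test is valid, and the gain depends on a correlation the protocol does not give

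*Protocol article*

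**What the plan says.** The Statistical analysis section fixes the primary test: "The primary analysis of the primary outcome will be conducted using t-tests of independent group mean differences in 6MWT". The SPIRIT table (Table 2, item 20a) has the same test, as "t-tests of independent group mean differences in 6MWT at each time point". Neither mentions a covariate.

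Baseline 6MWT is available for this purpose. Study objectives says "Cardiorespiratory fitness is assessed using a 6-min walk test (6MWT) at five timepoints in the trial", the first being baseline. The Missing data section adds: "By design, no data will be missing at baseline because only participants with complete baseline data will be randomised".

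The plan uses the baseline walk in three other ways:
- The paragraph that sets the primary test also plans t-tests on each participant's change from baseline.
- Item 20a uses the pooled baseline median as the cut-point for a binary outcome.
- The mixed-level analyses, labelled secondary, include the baseline score as a covariate.

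The endpoint is worded in two ways. The Primary outcome section reads as a value at one visit: "The primary outcome is measurement of cardiorespiratory fitness using the 6MWT assessed at the pre-surgery timepoint". SPIRIT item 12 reads as a change: "The primary endpoint is cardiorespiratory fitness measured by the 6-min walk test between the baseline assessment and the pre-surgery time point".

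**The concern.** The baseline walk is the same test in the same person. If it predicts the pre-surgery walk, an unadjusted comparison leaves that explained variation in the error term. The protocol already accepts baseline as a relevant covariate, but not in the test that decides the trial.

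The trial is small and has little power in reserve. With SD 85 m and 25 per arm, the chance difference between arms in mean baseline 6MWT has a standard error of 85 × √(2/25) = 24.0 m, over a third of the 67.5 m target. The part of any imbalance that correlates with the outcome passes into an unadjusted estimate. At stake are power and the width of the confidence interval, not validity.

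**Working it through.** **Inputs from the protocol article**
- Difference: 15% of 450 m = 67.5 m (Sample size calculation; SPIRIT item 14).
- SD: 85 m, from "a baseline score of 450 m (standard deviation 85 m" (SPIRIT item 14).
- Error rate and power: "value of 0.05 and power of 80" per cent (Sample size calculation). Sidedness is not stated.
- Sample: 26 with full data, 62 recruited, 20% dropout, 1:1 allocation.

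**Assumptions, not in the article**
- r, the correlation between baseline and pre-surgery 6MWT, run from 0 to 0.7.
- The 85 m baseline SD also holds at pre-surgery in both arms.

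**Step 1: reproduce the plan's figure.** Normal approximation, two-sided: n = 2 × (1.960 + 0.842)² × (85/67.5)² = 24.9, so 25 per arm. The noncentral t gives 25.9, so 26 per arm, with 80.2% power. One-sided testing would give 20 or 21. The stated 26 is therefore per group, for an unadjusted two-sided t-test.

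**Step 2: number analysed.** 62 × 0.8 = 49.6, about 25 per arm. There the plain t-test has 78.6% power.

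**Step 3: standard errors at n = 25 per arm**
- Plain t-test: 85 × √(2/n) = 24.0 m, on 2n − 2 = 48 degrees of freedom.
- Change-score t-test: 85 × √(2(1 − r)) × √(2/n), on 48 degrees of freedom.
- ANCOVA: 85 × √(1 − r²) × √(2/n) × √(1 + 1/(2n − 4)), on 2n − 3 = 47 degrees of freedom. The last factor (1.011) is the penalty for estimating the slope.

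Example, ANCOVA at r = 0.5: 85 × 0.866 = 73.6 m; × 0.2828 = 20.8 m; × 1.011 = 21.0 m. The 95% CI half-width is 2.012 × 21.0 = 42 m.

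**Step 4: results** (noncentral t, 67.5 m; plain t-test 78.6% power and half-width 48 m throughout)

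| r | Power, ANCOVA | Power, change t-test | Half-width, ANCOVA | Half-width, change |
|---|---|---|---|---|
| 0 | 77.7% | 49.4% | 49 m | 68 m |
| 0.15 | 78.6% | 56.0% | 48 m | 63 m |
| 0.3 | 81.4% | 64.3% | 47 m | 57 m |
| 0.4 | 84.3% | 70.9% | 45 m | 53 m |
| 0.5 | 88.1% | 78.6% | 42 m | 48 m |
| 0.6 | 92.5% | 86.8% | 39 m | 43 m |
| 0.7 | 96.8% | 94.4% | 35 m | 37 m |

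At the planned 26 per arm the pattern is the same: t-test 80.2%; ANCOVA 79.3% at r = 0, 82.9% at 0.3, 89.4% at 0.5 and 97.3% at 0.7.

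**Step 5: a smaller effect.** If the true difference is the 60 m gain that the article cites, the t-test at 25 per arm has 68.6% power, and ANCOVA about 80% at r = 0.5 and 92% at r = 0.7.

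**Step 6: value or change.** Change is the pre-surgery value minus baseline. With baseline in the model, switching the outcome from value to change lowers the baseline coefficient by exactly 1. The group coefficient, its standard error and its p-value stay the same.

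**The case against.** The strongest reply is that nothing here is wrong. A t-test is valid under 1:1 randomisation, and the sample size was built for it. Chance baseline imbalance adds variance that the 85 m SD already counts; it does not bias the test. This stands. A reader might infer from the table that the primary analysis is faulty or the trial underpowered because of it. The article does not support that: 26 per group gives the stated 80%, and the 78.6% comes from recruiting 62 with 20% dropout, which is a separate matter.

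A reader might also infer that baseline is ignored outside the secondary model. It is not: the primary-analysis paragraph plans change-score t-tests. If the change wording of SPIRIT item 12 governs, the primary test already uses baseline, and at r = 0.7 ANCOVA adds little (94% to 97%, 37 m to 35 m). ANCOVA is still ahead at every r tabulated, and far ahead when r is below 0.5.

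The size of the gain rests on r, which the article does not report. Neoadjuvant treatment falls between the two walks, and the Background says that it can affect fitness, so a high r cannot be taken for granted. This stands too, which is why a range is shown.

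Finally, a baseline-adjusted mixed model is already planned, so the adjusted estimate will be produced. But it is labelled secondary, and the trial's main claim rests on the primary test.

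**Conclusion.** The point holds as an efficiency improvement that should be made. Against the plain t-test at 25 per arm, ANCOVA adds about 3 points of power at r = 0.3, 6 at 0.4, 10 at 0.5 and 18 at 0.7. The 95% CI half-width falls from 48 m to 42 m at r = 0.5 and to 35 m at r = 0.7. Against the change-score t-test the power gain is about 17, 10 and 2 points at r = 0.3, 0.5 and 0.7. The gain over the plain t-test is thus small at r = 0.3 and clear from about 0.4.

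The change is not entirely free: it uses one degree of freedom, loses about one point of power at r = 0 and breaks even near r = 0.15. All figures rest on the assumed r and on carrying the 85 m baseline SD over to pre-surgery.

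**What to change.** State in the Statistical analysis section and in SPIRIT item 20a that the primary analysis is a linear model of pre-surgery 6MWT on randomised group and baseline 6MWT, reporting the adjusted mean difference with its 95% CI and p-value. Keep the unadjusted t-test as supportive. Make the change before the analyst sees allocation.

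Align the endpoint wording in the Primary outcome section and SPIRIT item 12. The adjusted model gives the same treatment estimate and p-value for value and change, but the two descriptions should still agree.

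The cost is about one sentence in each place and one degree of freedom. No extra data or participants are needed, and the sample size can stay as it is.

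### The secondary mixed model for 6MWT combines a baseline covariate with a difference-in-difference reading of the interaction; on neither available reading is that term a baseline-adjusted pre-surgery effect

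*Protocol article*

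**What the plan says.** The Statistical analysis section of the protocol article makes three statements about the secondary analysis of 6MWT:

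- Terms: "The secondary analysis of the primary outcome will use mixed-level analysis with intervention group, time point and interaction of intervention and time points".
- Baseline: "This analysis will include baseline score for the outcome measure as a covariate".
- Interpretation: "The estimated parameter for the interaction variables will be interpreted as the difference-in-difference between the two groups over time".

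Table 2 (SPIRIT item 20b) repeats all three. Under Study objectives, 6MWT is measured at five points: "baseline, post-NCT, pre-surgery, and 4 weeks and 10 weeks after surgery". The article does not say whether the baseline visit is one of the modelled time points, or which time point is the reference.

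The mixed model is not the primary analysis: "The primary analysis of the primary outcome will be conducted using t-tests of independent group mean differences in 6MWT". Change from baseline is also to be compared by t-tests. Table 2, item 7 places the primary hypothesis between the baseline and pre-surgery assessments.

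**The concern.** Using baseline as a covariate normally means that the responses begin at the first post-baseline visit. Reading the group-by-time interaction as a difference-in-difference from baseline requires baseline to be a response. The plan asks for both, so one coefficient is given a meaning that the covariate either changes or makes redundant.

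Two things are at stake. The mixed model is the only between-arm analysis of 6MWT described in the article that uses baseline as a covariate, and with about 26 participants per arm that adjustment is worth having. The interpretation rule is also fixed in advance, so an analyst who fits the usual covariate-adjusted model and follows the rule would report the wrong contrast for the pre-surgery question. Exercise starts before NCT where time allows and continues through it, so some benefit may already be present at post-NCT. On that fit, this part of the benefit goes into the group term and not into the interaction.

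**Working it through.** **Inputs from the article.** Mean and SD: "baseline score of 450 m (standard deviation 85 m" (Table 2, item 14). Target: 15% of 450 m = 67.5 m. Size: "a 15% difference can be detected with a *p* value of 0.05 and power of 80% with a sample of 26 participants with full data", read here as 26 per group.

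**Assumptions, not in the article.** Two-sided 5% level; equal SD at all visits; equal correlation rho between any two visits, taken as 0.5 and 0.7; complete data; the time course of benefit.

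**Step 1. The plan's own figure.** For a difference of 67.5 m with SD 85 m at 80% power, the t-based solution is 25.9 per group, so 26, with power 80.2%. The stated figure reproduces. It concerns the t-test and does not depend on the mixed model.

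**Step 2. Post-baseline visits as responses, baseline as covariate.** Let D(t) be the group difference at visit t, with post-NCT as the reference.

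- Group term = D(post-NCT).
- Interaction at pre-surgery = D(pre-surgery) − D(post-NCT).
- Effect at pre-surgery = group term + interaction = D(pre-surgery).

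Expected interaction by time course:

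| D(post-NCT) | D(pre-surgery) | Expected interaction |
|---|---|---|
| 67.5 m | 67.5 m | 67.5 − 67.5 = 0 m |
| 40 m | 67.5 m | 67.5 − 40 = 27.5 m |
| 0 m | 67.5 m | 67.5 − 0 = 67.5 m |

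Simulated random-intercept models (26 per arm, 150 trials per scenario) gave:

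| D(post-NCT) → D(pre-surgery) | rho | Interaction: mean, % significant | Group + interaction: mean, % significant |
|---|---|---|---|
| 67.5 → 67.5 m | 0.5 | 5.8 m, 5% | 66.7 m, 90% |
| 67.5 → 67.5 m | 0.7 | −1.9 m, 6% | 66.2 m, 95% |
| 40 → 67.5 m | 0.5 | 28.1 m, 25% | 69.4 m, 93% |
| 40 → 67.5 m | 0.7 | 27.1 m, 39% | 69.1 m, 96% |
| 0 → 67.5 m | 0.7 | 67.9 m, 98% | 68.2 m, 97% |

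With 150 trials these averages are rough. At rho 0.5 the interaction has a standard error of 23.6 m (Step 3 formula), so its simulated mean has a Monte Carlo error of 23.6/√150 = 1.9 m, and 5.8 m is about three such errors from zero. The algebra gives exactly 0, and the argument rests on the algebra.

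**Step 3. Baseline as both a response and a covariate.** With baseline as the reference visit, interaction at pre-surgery = D(pre-surgery) − D(baseline), which is the difference-in-difference. In the simulated complete data it matched the raw difference in mean change to within 1e-11 m in every trial, so the covariate did not alter it. For a constant 67.5 m benefit it averaged 66.2 m (81% significant) at rho 0.5 and 66.7 m (93%) at rho 0.7.

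Large-sample precision with n per arm:

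- Change-score contrast: variance = (2·SD²/n) × 2(1 − rho).
- ANCOVA: variance = (2·SD²/n) × (1 − rho²).
- Ratio = 2(1 − rho)/[(1 − rho)(1 + rho)] = 2/(1 + rho).

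With n = 26 and SD = 85 m, √(2·85²/26) = 23.6 m.

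| rho | SE, change score | SE, ANCOVA | Variance ratio |
|---|---|---|---|
| 0.5 | 23.6 × √1.00 = 23.6 m | 23.6 × √0.75 = 20.4 m | 2/1.5 = 1.33 |
| 0.7 | 23.6 × √0.60 = 18.3 m | 23.6 × √0.51 = 16.8 m | 2/1.7 = 1.18 |

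**The case against.** The strongest reply is that the wording favours the second reading. Five 6MWT time points are listed, with baseline among them; the preceding paragraph of the analysis section works with change from baseline; and the hypothesis runs from baseline to pre-surgery. On that reading the interaction is the intended quantity and estimates the benefit without bias. **This stands.** A reader might infer that once baseline is a covariate the interaction cannot be the treatment effect. The article does not support so general a claim, because it never says that the baseline visit is left out of the responses. What remains on this reading is a covariate that does no work for the reported term and a loss of precision.

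A second reply is that an interaction of zero needs the first reading and a constant benefit together. **This also stands.** The article gives some reason to expect benefit to grow: intensity is not progressed during NCT but is progressed between NCT and surgery, and session frequency goes from two to three per week to three. The more general statement is that the interaction understates the pre-surgery effect by whatever benefit is already present at post-NCT.

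A third reply is that on the first reading the interaction is still a difference-in-difference over time, and that the plan never calls it the pre-surgery effect or says the group term will be ignored. That is literally so. But it is the only term given an interpretation, and a change since post-NCT does not answer the stated hypothesis.

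Finally, responses, reference visit and target contrast are details that a condensed article may leave to a fuller document. That would excuse silence. Here the article states an interpretation rule, in two places, that does not fit the covariate stated beside it.

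**Conclusion.** The point holds as an inconsistency in the secondary analysis of 6MWT. On one reading the designated term is the change in the group difference since post-NCT. It falls short of the pre-surgery effect by the benefit already reached at post-NCT: by all of it if the benefit is constant, by 40 m of 67.5 m in the intermediate scenario, and by nothing if no benefit exists at post-NCT. On the other reading the term is the correct difference-in-difference but carries no baseline adjustment, with variance 1.33 times (rho 0.5) or 1.18 times (rho 0.7) that of ANCOVA.

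The sizes rest on assumed correlations, equal SDs and assumed time courses. The exact equality with the change-score contrast was checked for complete data only, whereas the plan expects 20% drop-out.

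A reader might go further and infer that the trial could miss a real benefit because of this rule. The article does not support that. The primary t-test and the t-tests of change from baseline are separate analyses that would still show a stable benefit, and the sample size does not rest on the mixed model. The correction should be made, but it does not touch the primary inference.

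**What to change.** Choose one specification and state it identically in the Statistical analysis section and in Table 2, item 20b.

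- **(a) Baseline as covariate.** Responses are the four post-baseline visits; covariates are baseline 6MWT and baseline-by-visit. Report the adjusted group difference at each visit (group plus group-by-visit), with pre-surgery first. Delete the sentence that reads the interaction as the difference-in-difference.
- **(b) Baseline as response.** Responses are all five visits, with a common baseline mean for both arms. Drop the baseline covariate and report group-by-visit at pre-surgery. The common mean is justified by randomisation and is what brings in the baseline adjustment; dropping the covariate alone would leave the unadjusted change-score contrast.

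The cost is about two sentences of text in each place. Both forms use measurements already scheduled, and neither changes the primary analysis or the sample size.
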